### Relevant concomitant care permitted or prohibited during the trial {11d}

As per the inclusion and exclusion criteria, the participant must have had a stable dose of any psychotropic medication for at least 4 weeks prior to study entry, and no other ongoing trauma-focused CBT or eye movement desensitization and reprocessing therapy is permitted during the trial. Data on any potential alterations to medication or the initiation of trauma-focused CBT or Eye Movement Desensitization and Reprocessing therapy will be collected during the follow-up assessment.

### Provisions for posttrial care {30}

At the end of the study, participants assessed as in need of further treatment will be helped in finding other adequate treatments.

### Outcomes {12}

The primary outcome measure is the CAPS-5, the gold-standard clinical interview that evaluates the severity of PTSD symptoms and determines the presence of PTSD in the past month [12]. This evaluation will be conducted at multiple time points: upon enrollment, 1 month after completing the treatment (primary endpoint), and during the 6- and 12-month follow-up assessments. The CAPS-5 total severity score has been shown to exhibit strong internal consistency (Cronbach’s *α* = 0.88) and interrater reliability (intraclass correlation coefficient = 0.91), along with favorable test–retest reliability (intraclass correlation coefficient = 0.78) [12]. Treatment response will be considered achieved if there is a minimum of 10 points improvement on the CAPS-5 between baseline and the participant’s last available measurement within the baseline to 12-month follow-up period (adapted from [13]). Remission will be defined as the absence of a PTSD diagnosis or a CAPS-5 total symptom severity score below 12 [13]. To be classified as having achieved recovery, participants must maintain their remission status at both the 6-month and 12-month follow-ups.

Secondary self-rated outcome measures include the Posttraumatic Stress Disorder Checklist for DSM-5 (PCL-5) [14] and the International Trauma Questionnaire (ITQ) [15] to capture self-rated symptoms of PTSD and complex PTSD. The Patient Health Questionnaire (PHQ-9; [16]) and the EuroQol 5-dimensions (EQ-5D; [17]) will be used to assess the level of depressive symptoms and quality of life. Treatment response on the PCL-5 will be defined as a drop of 10 points or more. For remission, a score below 30 will be used, which has been identified as indicative of probable PTSD in the Swedish version of the PCL-5 [18].

To calculate quality-adjusted life-years for cost-utility analysis, participants will complete the Assessing Quality of Life 6 Dimensions (AQoL-6D; [19]). Data concerning the utilization of medical resources, medication, social care, absenteeism, and presenteeism in relation to employment will be collected using The Treatment Inventory of Costs in Patients with psychiatric disorders (TIC-P; [20]). Moreover, information on adverse events will be gathered using the Negative Effects Questionnaire (NEQ) immediately after treatment completion and the upcoming assessment points [21]. Participants will also receive an open-ended question asking for the occurrence of adverse events weekly during treatment.

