## Interventions

### Explanation for the choice of comparators {6b}

The trial will compare therapist-guided digital prolonged exposure (HOPE) to a digital therapist-guided active control condition to assess its efficacy. A matched digital comparator preserves parity in modality, platform, therapist contact, and expectancy, enabling estimation of the incremental benefits and potential adverse effects attributable to trauma-focused exposure. The comparator includes psychoeducation, stress-management skills, and supportive therapist contact, and explicitly excludes imaginal and in vivo exposure and other trauma-focused techniques. After the 1-month post-treatment follow-up (primary endpoint), participants may access the alternative condition without therapist guidance. This timing preserves the integrity of the primary endpoint while improving ethical access.

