## Statistical methods

### Statistical methods for primary and secondary outcomes {20a}

The data analyses will be carried out by an independent statistician who is not part of the research group. This statistician will also remain blind to the group allocation throughout the duration of the trial. The intention-to-treat approach to the analysis population will be applied in all cases unless specified otherwise. The significance level for all statistical tests will be *α* = 0.05.

For our primary research questions, we will fit a linear mixed-effects model for repeated measures to evaluate change in CAPS-5 total scores within and between groups over time. Fixed effects will include treatment, time, and the treatment × time interaction; a participant-specific random intercept will be specified. An unstructured within-participant covariance will be used, allowing distinct correlations between all pairs of time points. The model will be estimated by restricted maximum likelihood and will use all available observations, yielding unbiased estimates under missing at random or missing completely at random assumptions. The primary hypothesis will be tested two-sided at *α* = 0.05. No adjustments will be made for multiplicity.

As a complementary check at the primary endpoint, we will fit a linear regression of change in CAPS-5 from baseline to 1-month on randomization arm, adjusting for baseline CAPS-5.

We will report within- and between-group effect size (Cohen’s *d*) with 95% CIs. Effects will be deemed statistically significant at *p* < 0.05. Magnitudes will also be described using conventional benchmarks: small (0.20), medium (0.50), large (≥ 0.80).

Crossover participants continue all scheduled outcome assessments. Post-crossover data are obtained as part of a naturalistic follow-up.

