### Adverse event reporting and harms {22}

Participants can report the occurrence of undesirable treatment effects at any point through the study period by alerting the designated therapist on the digital platform or assessor or contacting the study personnel. Weekly measures to capture any unwanted adverse events will be administered, including questions about intensity, duration, and characteristics of the adverse event.

All potential undesirable treatment effects will be categorized by the investigator into three levels: mild, moderate, or severe. An event will be deemed serious if it poses a life-threatening risk, leads to death, causes persistent or significant disability/incapacity, necessitates hospitalization or its prolongation, or is determined to be medically significant by the principal investigator. The Negative Effects Questionnaire (NEQ) will be utilized posttreatment and during follow-ups to systematically gather data on potential adverse effects.

Therapists will be needed to promptly inform the principal investigator if they have concerns that a participant has caused, or is at risk of causing, significant harm to themselves or others or discloses any suicidal ideation. In such cases, a suicide risk assessment will be conducted over the phone to ensure appropriate and immediate support.

All participants in the study will receive active treatments with previous support by clinicians who specialize in the treatment of PTSD. Previous studies that have investigated intensive prolonged exposure have not detected any serious adverse events. The additional risks associated with participating in digital HOPE are hence considered to be small. All participants will be closely monitored during the study, and additional treatment will be provided in case of an unlikely severe deterioration.

Excluded participants will be informed where to seek help in the regular health care system. After the 1-month follow-up, participants will be offered the treatment they were not originally allocated to.

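### CAPS-5 response is scored at the last available visit up to 12 months, so the by-arm comparison mixes data from before and after participants could take up the other programme and does not isolate HOPE against control

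*Protocol article*

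**What the plan says.** Outcomes {12} of the protocol article sets the threshold: "Treatment response will be considered achieved if there is a minimum of 10 points improvement on the CAPS-5", counted from baseline to the participant's "last available measurement within the baseline to 12-month follow-up period". CAPS-5 is taken "upon enrollment, 1 month after completing the treatment (primary endpoint), and during the 6- and 12-month follow-up assessments". Recovery is stricter: "participants must maintain their remission status at both the 6-month and 12-month follow-ups". Remission is defined by diagnosis or score and is not tied to a visit.

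The choice-of-comparators section {6b} states: "After the 1-month post-treatment follow-up (primary endpoint), participants may access the alternative condition without therapist guidance". It says this timing protects the primary endpoint. The harms section {22} repeats the offer for both arms: "After the 1-month follow-up, participants will be offered the treatment they were not originally allocated to".

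The statistical methods section {20a} keeps participants who switch in all assessments and adds: "Post-crossover data are obtained as part of a naturalistic follow-up". The trial design section {8} also calls the 6- and 12-month visits naturalistic. The subsection on secondary outcomes plans logistic models and odds ratios for binary outcomes, with chi-square or Fisher tests for cross-sectional comparisons, and classes every secondary analysis as exploratory. Section {20b} plans logistic regression for prognostic models of CAPS-5 response.

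**The concern.** The design protects the randomised comparison up to the 1-month visit and treats what follows as naturalistic. The only CAPS-5 response definition in the article ignores that boundary. It takes whichever visit happens to be last, and for a participant who stays in the study that is the 12-month visit. A control participant who improves after working through HOPE then counts as a control responder.

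The visit used also depends on retention. Someone lost after 1 month is scored before the switch, and someone never assessed after baseline can be scored against baseline and so cannot respond. Two participants with the same course can be classified differently because one stayed longer.

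Responder rates are what clinicians tend to quote, and the Discussion says the trial may influence guidelines. A responder odds ratio scored this way would invite a reading as the effect of HOPE against control, which it does not isolate.

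**Working it through.** **Which visit is scored.** From the CAPS-5 schedule and the timing of the offer:

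| Last CAPS-5 available | Visit used for response | Relation to the offer |
|---|---|---|
| 12 months | 12 months | after |
| 6 months | 6 months | after |
| 1 month | 1 month | before |
| none after baseline | baseline | before; change is 0, so non-response |

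Recovery needs the 6- and 12-month visits, both after the offer. Nothing in the article gives a 1-month CAPS-5 response or limits response to data from before a switch.

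Enrolment date can enter too. Trial status says analysis and reporting begin once all primary-endpoint data are in, with inclusion from September 2023 to August 2026 and last follow-up in October 2027. If response were scored at that point, early participants would have a 12-month value and the latest only a 1-month value.

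**The plan's own figure.** The article states no response rate. Its sample size (Sample size {14}) supplies the effect size and the number analysed. With d = 0.35, two-sided alpha 0.05 and 80% power, n = 2(1.96 + 0.842)²/0.35² = 128.2, so 129 per arm, as stated; power at 129 is 80.3%. Inflation gives 129/0.9 = 143.3, against 143 stated, which is within rounding. This figure concerns the 1-month mean difference and is not affected.

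**Illustration of dilution.** From the documents: d = 0.35 and 129 per arm. Assumed, because the documents do not give them:
- control response at 1 month, pC: 30% to 50%
- HOPE response from a normal shift: pT = Φ(Φ⁻¹(pC) + 0.35)
- share with a CAPS-5 after 1 month, f: 0.9
- share of controls taking up HOPE, u: 25% to 75%
- fraction of the HOPE benefit they gain, g: 0.5 to 1.0 (below 1 because the programme is then unguided)
- HOPE arm unchanged after 1 month

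Control response at the last visit is pC + f·u·g·(pT − pC), so the difference is multiplied by 1 − f·u·g.

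For pC = 0.40, pT = Φ(−0.253 + 0.35) = 0.538, a difference of 0.138.

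| Scoring | Factor | Control | Difference | Odds ratio | Power, 129 per arm |
|---|---|---|---|---|---|
| 1 month | 1 | 0.400 | 0.138 | 1.75 | 61% |
| last visit, u = 0.25, g = 0.5 | 1 − 0.1125 = 0.8875 | 0.416 | 0.123 | 1.64 | 51% |
| last visit, u = 0.50, g = 1.0 | 1 − 0.45 = 0.55 | 0.462 | 0.076 | 1.36 | 23% |
| last visit, u = 0.75, g = 1.0 | 1 − 0.675 = 0.325 | 0.493 | 0.045 | 1.20 | 11% |

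Across pC = 0.30 to 0.50 the 1-month difference is 13 to 14 points (odds ratio 1.75 to 1.77, power 59% to 61%). Scored at the last visit, it runs from about 12 points (odds ratio about 1.65, power about 50%) down to about 4 points (odds ratio about 1.2, power about 10%). With no uptake the two scorings agree.

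**Baseline-only participants.** If a share m of an arm has only a baseline CAPS-5 and is scored as non-responding, that arm's rate becomes (1 − m)p. With m = 0.10 in both arms, borrowing the 10% attrition planned for 1 month and assuming that none of these participants returns later, the 0.138 difference becomes 0.9 × 0.138 = 0.124. With unequal shares the difference changes by mC·pC − mT·pT. It is inflated in favour of HOPE whenever mC·pC exceeds mT·pT.

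**The case against.** The strongest defence is that little hangs on this. The primary outcome is 1-month CAPS-5 severity, secondary analyses are declared exploratory, and the later visits are openly labelled naturalistic. Remission and PCL-5 response are not tied to the last visit, so categorical results at 1 month remain possible. All of this stands and limits the severity. It does not repair the CAPS-5 response definition, which draws on the naturalistic data without separating them.

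Several stronger readings are tempting and are not supported:

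- *Response and recovery both lie wholly after the offer.* That is exact only for recovery. Response can be scored at 1 month or at baseline.
- *The arms are no longer comparable at all.* The article says "participants may access the alternative condition without therapist guidance", so switching is optional and unguided. A by-arm contrast still compares randomised groups, as HOPE first against control first with optional switching. That is a legitimate question, but a different one.
- *The bias must run toward no effect.* Dilution is likely, but differential dropout could push the other way, and participants in the HOPE arm may switch too.
- *The plan has no method for an outcome with one value per person.* It does: chi-square or Fisher tests under the secondary analyses, and ordinary logistic regression in {20b}.

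Recovery means sustained remission, so it cannot be scored at 1 month, and no sentence claims a HOPE-versus-control effect on it specifically. Only the general rule on odds ratios reaches it.

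The analysis plan on OSF is not shown and may add per-visit rules. The definition in the article is nevertheless explicit and is wrong as written.

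**Conclusion.** The point holds for the CAPS-5 response definition, which is wrong as written. Followed literally, it combines visits from before and after the offer according to who stayed in the study, and its by-arm odds ratio does not isolate HOPE against control. Recovery rests entirely on visits after the offer and should be read accordingly.

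The effect is probably dilution: in the illustration, from 13 to 14 points down to between about 12 and 4. That range rests on assumed response rates, uptake and benefit, with the HOPE arm held fixed. The true size depends on crossover uptake and differential dropout, neither of which the documents give.

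This should be fixed, but it is not critical: the primary 1-month severity analysis is unaffected.

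**What to change.** In Outcomes {12}, define CAPS-5 response for the between-arm comparison as an improvement of at least 10 points from baseline to the 1-month primary endpoint, and score remission for that comparison at the same visit. Delete the last-available-measurement rule. Handle missing 1-month values by a model or by multiple imputation, so that an absent visit is not counted as non-response by default. The prognostic models in {20b} would then use the same 1-month definition.

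Report response at 6 and 12 months, and recovery, per visit as naturalistic results with crossover uptake by arm. If a by-arm contrast is wanted there, label it HOPE first against control first.

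The cost is wording in the article and the OSF plan, settled before unblinding so that the visit is not chosen after seeing results. The 1-month CAPS-5 is already collected, and neither new data nor a larger sample is needed. The downside is that later response and recovery lose any claim to a HOPE-versus-control effect.

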### Eligibility criteria {10}

We will employ broad eligibility criteria to maximize the external validity of the study. Participants with comorbid conditions, such as neuropsychiatric disorders, depression, and substance abuse, will be considered for inclusion provided they meet all other inclusion/exclusion criteria, with PTSD being their primary diagnosis. Eligibility is determined via a two-stage process: (1) a participant-completed web-based screening battery for common mental disorders (including PTSD symptoms, depression/anxiety, alcohol/drug use, psychosis/mania, and suicidal ideation), followed by (2) a clinician-administered diagnostic assessment to confirm PTSD and evaluate risk.

Please see Table 1 for the full inclusion and exclusion criteria.

**Table 1 Tab1:** Inclusion and exclusion criteria

**Inclusion criteria**	≥ 18 years of age
	Primary diagnosis of PTSD according to the Diagnostic and Statistical Manual of Mental Disorders, fifth edition (DSM-5)
	Signed informed consent
	Have had a stable dose of any psychotropic medication for at least 4 weeks prior to study entry
	Being fluent in Swedish
	Daily access to a computer or device with internet connection
**Exclusion criteria**	PTSD is not the primary concern
	Serious mental health symptoms, such as mania, psychosis, alcohol, or substance use disorders or current suicide risk warranting immediate clinical attention
	Ongoing trauma-focused CBT or Eye movement desensitization and reprocessing therapy
	Ongoing trauma-related threat (e.g., living with a violent spouse)

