#### Treatment variables

Data will also be collected on the number of completed modules, dropouts of treatment, sent messages, and therapist time spent in the digital platform for each participant and any additional time needed, for example, phone calls outside the platform. A treatment completer is defined as a participant who completed all treatment modules or responded early. Early recovery is defined as the participant showing a positive response after completing at least 3 modules, with a minimum of a 10-point reduction on the PCL-5 or achieving a total sum score below 30, and both the participant and therapist agreeing to conclude the treatment. Participants who discontinue treatment or experience early recovery will be encouraged to continue their participation in the remaining outcome assessment points.

Ratings on the subjective units of distress (SUD) will be collected during exposure exercises (pre, during, post and maximum), and harm expectancies will be assessed using digital worksheets. The Credibility/Expectancy Questionnaire (CEQ; [22]) and Working Alliance Inventory–Short Form Revised (WAI; [23]) will be utilized to assess treatment credibility and working alliance between the treatment arms.

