## Assignment of interventions: allocation

### Sequence generation {16a}

After eligibility confirmation and baseline assessment, participants will be randomized 1:1 to HOPE or the active control, stratified by self-rated complex PTSD (yes/no) and gender. The sequence is computer-generated with variable block sizes and programmed by an external unit (Karolinska Trial Alliance) via a secure, audited, web-based system independent of the clinical team. The sequence is stored server-side and inaccessible to site staff. Allocation is released only after baseline completion through role-based login, ensuring concealment; staff cannot foresee upcoming assignments. On randomization, the system issues a tamper-evident allocation certificate (participant ID, assigned arm, personnel ID, timestamp) and maintains a full audit trail.

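### PCL-5 remission is defined only as a score below 30, with no PCL-5 entry minimum, so people already below 30 at baseline inflate the reported remission percentages in both arms

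*Protocol article*

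**What the plan says.** In Outcomes {12} the protocol article gives two PCL-5 classifications. Response is a change: "Treatment response on the PCL-5 will be defined as a drop of 10 points or more". Remission is a state: "For remission, a score below 30 will be used". The same sentence explains the number 30 as the Swedish cut-off for probable PTSD. The remission rule refers neither to the baseline score nor to change.

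Entry does not depend on the PCL-5. Under Eligibility criteria {10}, a web screen is followed by "a clinician-administered diagnostic assessment to confirm PTSD and evaluate risk". The reader is then told: "Please see Table 1 for the full inclusion and exclusion criteria". Table 1 asks for a primary DSM-5 diagnosis of PTSD and contains no PCL-5 minimum.

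The statistical methods apply intention to treat unless stated otherwise, and nothing in the article limits the PCL-5 remission outcome to a subset. Secondary analyses are labelled exploratory.

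**The concern.** Remission from probable PTSD presupposes having been above the probable-PTSD cut-off. For the CAPS-5 this is largely secured, because entry requires the diagnosis. For the PCL-5 nothing secures it: a clinician can confirm PTSD in someone whose self-report is below 30, and eligibility is deliberately broad. Such a person who scores 28 before and 28 after treatment is counted as a PCL-5 remission.

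What is at stake is the percentage that readers will quote. A remission rate for HOPE or for the control arm that includes people below the cut-off before treatment overstates how many moved out of probable PTSD during the trial.

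**Working it through.** **The rule itself.** Baseline 28, follow-up 28: 28 < 30, so the participant is remitted. This needs no numerical assumption.

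**Plan figures.** The article gives no PCL-5 remission rate or baseline PCL-5 distribution to reproduce. Its 129 per arm for the primary endpoint is used below only as a denominator. It reproduces: 2 × (1.96 + 0.8416)² / 0.35² = 128.1, rounded up to 129.

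**How many could start below 30.** Assumption: whole-number scores from a roughly normal distribution, so the share is f = Φ((29.5 − mean)/SD).

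| Assumed mean | Assumed SD | f | Of 286 |
|---|---|---|---|
| 45 | 12 | 9.8% | 28 |
| 45 | 15 | 15.1% | 43 |
| 50 | 12 | 4.4% | 13 |
| 50 | 15 | 8.6% | 25 |
| 55 | 12 | 1.7% | 5 |
| 55 | 15 | 4.5% | 13 |

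**Effect on the percentages.** Remission in all randomized equals (1 − f) × rate among those starting at 30 or above + f × rate among those starting below 30. The excess over the restricted rate is therefore f × (low-starter rate − restricted rate).

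Central illustration, all assumed: baseline mean 50, SD 15; follow-up SD 16; correlation 0.5; control change 12 points; HOPE better by 0.35 × 16 = 5.6 points for everyone; bivariate normal.

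- Control, all randomized: Φ((29.5 − 38)/16) = 29.8%. Starting at 30 or above: 26.3%. Low starters: 66.6%. Excess: 0.0859 × (0.666 − 0.263) = 3.5 points.
- HOPE, all randomized: Φ((29.5 − 32.4)/16) = 42.8%. Starting at 30 or above: 39.4%. Low starters: 79.5%. Excess: 0.0859 × (0.795 − 0.394) = 3.4 points.
- Raw odds ratio: 1.77 in all randomized, 1.82 restricted.

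**Range.** The grid takes the means and SDs above, correlations of 0.3, 0.5 and 0.7, and control changes of 8, 12 and 16 points:

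- excess remission of 0.4 to 8.3 points (control) and 0.5 to 7.9 points (HOPE);
- raw odds ratio lower by 0.01 to 0.17, that is, log odds ratio lower by 0.004 to 0.09. The standard error of the log odds ratio in the central illustration, with 129 per arm, is about 0.26.

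These are raw two-by-two odds ratios, not output of the mixed-effects logistic model that the article plans.

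**The case against.** **Remission as a state is a coherent quantity.** The proportion below the probable-PTSD cut-off at follow-up can legitimately be reported. This stands to the extent that the all-randomized figure should be kept. It does not make that figure a remission rate in the ordinary sense without knowing how many were below 30 at the start.

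**The planned model deals with part of it.** If baseline enters the mixed-effects logistic model as it does the primary model, someone already below 30 is recorded as such at baseline. That may absorb some of any dilution of the odds ratio. It does not correct the reported percentages.

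**The full analysis plan on OSF may restrict the denominator.** It may, and it is not shown here. The point rests on the definition that the article does state.

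**Few may be affected.** The Discussion speaks of moderate to severe PTSD, which would favour the low end of the range. The article does not settle this.

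Three stronger readings are tempting, and the article does not support them.

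- A reader might infer that the response and remission rules contradict each other, because the 28-to-28 participant is remitted and a non-responder. They measure different things, change and state. The discordance also survives any restriction on baseline: a fall from 31 to 29 is remission without response. In the central illustration about a third of remitted non-responders in the control arm started at 30 or above.
- A reader might infer that the early-recovery rule under Treatment variables has the same fault, since it accepts "with a minimum of a 10-point reduction on the PCL-5 or achieving a total sum score below 30". That rule begins "Early recovery is defined as the participant showing a positive response after completing at least 3 modules" and needs agreement of participant and therapist. The wording already implies change, so no misclassification is shown and no edit is asked for.
- A reader might infer bias in favour of HOPE. Baseline precedes allocation, so low starters should be balanced between arms on average. The rule raises both percentages and, if anything, dilutes the contrast slightly.

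**Conclusion.** The point holds as a minor one. As written, the rule counts as remitted people who were never above the cut-off on the PCL-5, and this inflates the reported PCL-5 remission percentages in both arms. The existence of the problem follows from the text alone. Its size does not: about 2% to 15% starting below 30, and about 3.5 points of excess remission per arm in the central illustration, rest on assumed means, SDs, correlation and change. The effect on the raw odds ratio is small, at most about a third of its standard error (0.09 against 0.26). The outcome is exploratory, and neither the CAPS-5 primary analysis nor PCL-5 response is affected.

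**What to change.** Report PCL-5 remission among participants with baseline PCL-5 of 30 or more, give the all-randomized result alongside, and state the number below 30 at baseline in each arm. The restriction respects randomization, because "Allocation is released only after baseline completion through role-based login", and Table 2 lists the PCL-5 at baseline. Participants already enrolled can be classified, so only the wording of the definition changes.

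The cost is a smaller denominator for one exploratory contrast: 129 × (1 − f), or about 123, 116 and 110 per arm if 5%, 10% and 15% start below 30. Power for the raw contrast may move either way: from 58.8% to 57.0% in the central illustration, and by −6.3 to +1.8 points across the grid. Keeping the all-randomized result limits that cost.
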